#### Device failure

Device failures and risks would be for example lack of safety audit feed although the patient had >2 symptoms during the 6-MWT or during an exercise or although the patient trains outside the defined thresholds (ongoing quality management during the trial by screening the database). Others are lack of exercise transferal into the database, interruption of exercises without a clear reason, or non-storage of data in the database.

#### Reasons to interrupt the trial

An interruption of the trial is used to implement corrective measures and evaluate their effectiveness. If the corrective actions fail, trial termination will be the next step.

All known or foreseeable factors that may impair the clinical trial and its interpretation:More than 15% of patients are lost to follow-upMore than 60% of exercises are not performedGenerally bad recruitmentDSMB concerns during the trialLack of financing or budget issues

The first 3 factors are associated with penetration and acceptance of the clinical trial. As it is a new digital therapy, this is a challenge. However, the time for digital therapies is now, the study group has repeatedly proven to be able to perform high-quality clinical trials with and without digital therapies, and we have a special approach to recruitment supported by the study group. There may of course be a situation in which the digital therapy in the interventional groups ends signals that tell us to stop or require an adjustment of the protocol. This is completely unforeseeable currently. However, as we have already performed a sound pilot trial, we do not expect critical deviations from our risk-benefit statement. Budgeting and financing may be critical if we have a major deviation and requirement to adapt the protocol.

Strong reasons to terminate the trial at individual sites are:A significant misconduct of the PI at a specific siteRepeated violations and significant non-compliance with the protocol at specific sites that do not improve even after preventing and correcting actions including team trainingMissing ongoing documentation in the eCRFMissing vigilance reporting from the site to the sponsor and authoritiesThe fact or suspicion that there is an unacceptable high risk that cannot be mitigated by any measure or intervention of risk by the risk management team into an acceptable risk. This includes an unacceptable health risk or the advisory of the IRB or any regulatory body involved.

In case of an interruption, the sponsor guarantees to provide resources for the follow-up of the patients in the trial as planned. Study participating centers and patients will immediately be informed by the sponsor (main investigator) about the interruption/termination. The sponsor will further inform the IRB and regulatory authorities.

### Strategies to improve adherence to interventions {11c}

We conduct the study in a window of opportunity for life changes in patients before surgery, which should lead to high compliance. Furthermore, the gamification via app use and vibration/colorful display of correct heart frequency ranges should improve adherence. There is a hotline to the treating hospital for every patient.

Measures to enhance adherence:Clear planning of the stepwise approach in the Clinical Evaluation PlanStudy group support from the sponsor to have smooth onboarding and establishment of screening, recruiting, and compliance within the study (reduce barriers approach)Multiple telephone/mail contacts with the trial participantsSafety by design and convincing usability of the devicesLow documentation workload for the centers considering the items required in the eCRFProvision of a dedicated quality management and risk management group

### Relevant concomitant care permitted or prohibited during the trial {11d}

All other necessary therapies for enrolled patients, for example, neoadjuvant therapy, are allowed if the inclusion criteria are met.

### Provisions for post-trial care {30}

After surgery, patients will undergo follow-up assessments on days 7 and 90 to evaluate the occurrence of any (serious) adverse events. One year after surgery, the patient’s status will be evaluated again. The end of the trial is defined as the last 1-year follow-up of the last patient.

Trial-related harm will be covered by a study-specific insurance policy. Safety protocols embedded in The Prehab App will address foreseeable risks, with safety issues monitored, documented, and reported as necessary. The insurance was purchased at HDI Global SE (Nr. 570 10320/03014/03537) with a coverage of 500,000€ per participant and a maximum coverage of 50,000,000€ for all participants in the clinical investigation.

Patients will all be treated in accordance with the local standard after the trial has been terminated. There is no further requirement to specifically adapt after treatment to the trial-specific treatment. All data will be stored in the eCRF as outlined in the Appendix of the documents. The data collected with the app will be stored in an ISO 27001-certified cloud of a server provider located in Germany. The eCRF data will be stored in the Secutrial ® eCRF system which is a regulatory-cleared provider with servers in Germany.

### Outcomes {12}

#### Descriptive measures, survival analyses, and cost analyses

Primary outcome: occurrence of any postoperative complication within 90 days after surgery according to the Clavien–Dindo classification (grades I–V).

Secondary outcomes: 1-year overall survival, 6-min walking distance, QLQ-C30 quality of life score, adherence and compliance, device failures, length of stay, days on ICU/IMC, readmission rates, hospital costs.

There will be an intention to treat analysis of all included patients fulfilling the in- and exclusion criteria. Data will undergo descriptive evaluation and assessment for normal distribution utilizing the Kolmogorov–Smirnov test with Lilliefors correction. Results will be presented as median or mean with standard deviation and interquartile ranges, and/or odds ratios with 95% confidence intervals, where applicable. Survival data will be computed as the time interval from the date of surgery to the date of death, or until censoring if patients are alive at their last visit/contact.

An intention-to-treat analysis will encompass all enrolled patients meeting the predetermined inclusion and exclusion criteria. Additionally, a per-protocol analysis will be conducted.

Compliance analysis in the intervention group includes the analysis of the number of exercises performed and the exercising within the predefined thresholds. We do expect a total of 191 6-MWTs delivering 65,000 pulse points and approximately 53 Mio. pulse points from 191 patients performing 10 exercises of 47 min each during the program that will define compliance as outlined in the following. Compliance of patients in the intervention group will be categorized according to the app algorithm (green: >75% of exercises performed and >75% of all measured values are green or yellow, yellow: 50–75% of exercises performed and 50–75% of all measured values are green or yellow, red: <50% of exercises performed and <50% of all measured values are green or yellow). Comparative compliance in the control group and the intervention group will be based on a descriptive comparison of the weekly safety calls in each group during the interventional phase as PROM analysis.

Surgical procedures and indications will be categorized based on OPS and ICD-10 codes. Subgroup analyses will be conducted using chi-square testing, *T*-testing, Kaplan–Meier survival analysis, and multivariate regression analysis.

Costs will be derived from data recorded in the electronic case report form (eCRF). Costs for a day on ICU are 1500€/day, for a day on the IMC 1000€, and on general ward 500€. The DRG generated by each case will be subtracted from the sum on each treatment unit and the final sums compared between the arms. The cost analysis will be conducted from the hospital/provider perspective based on in-hospital resource utilization including ICU, IMC, and general ward stay.

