## Abstract

**Background:**

Recent studies have demonstrated significant benefits associated with prehabilitation prior to major surgery. However, digital solutions in this domain are currently lacking. Our previous study, the Protego Maxima trial, reported positively assessed usability, validity, and safety of a prehabilitation application. In this randomized-controlled multicenter study, we aim to ascertain whether a digital prehabilitation program can reduce perioperative morbidity and costs in patients undergoing major surgery.

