### Trial design {8}

The LUMOS trial is a prospective and randomized-controlled trial. Here, a 3-to-6-week interventional digital prehabilitation program (The Prehab App and medical guidance) with a digitized informational app (Ready4Op) will be compared against a control group receiving only the informational application as a parallel group. The patient allocation ratio is 1:1. The framework of the trial is superiority.

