## Statistical methods

### Statistical methods for primary and secondary outcomes {20a}

Data will be analyzed using IBM SPSS (version 29 or more current version, if applicable). Surgical procedures and indications will be categorized based on OPS and ICD-10 codes. Subgroup analyses will be conducted using chi-square testing, *T*-testing, Kaplan–Meier survival analysis, and multivariate regression analysis. The center will be included as a stratification variable. Data will be descriptively evaluated and tested for normal distribution with the Kolmogorov–Smirnov test with Lilliefors correction. Data will be expressed as median or means with standard deviation and interquartile and/or odds ratios with 95% confidence intervals where appropriate. Survival data will be calculated as time intervals from the date of their death to the date of operation, respectively be censored, if they are alive at their last visit/contact. Subgroup analyses will be conducted for predefined categories including cancer versus non-cancer surgery, abdominal versus non-abdominal procedures, and higher-risk versus lower-risk patients. Surgical category will additionally be included as a covariate in multivariable analyses to account for potential heterogeneity in baseline risk. The primary analysis will follow the intention-to-treat principle. Multivariable regression models will be used to assess treatment effects while adjusting for study center and relevant baseline characteristics. Where appropriate, mixed-effects regression models including study center as a random effect will be applied to account for the multicenter study design.

Costs will be derived from data recorded in the electronic case report form (eCRF). Costs for a day on ICU are 1500€/day, for a day on the IMC 1000€, and on general ward 500€. The DRG generated by each case will be subtracted from the sum on each treatment unit and the final sums compared between the arms. This is a two-sided approach using *T*-testing of two independent groups and a *p *value < 0.05 is regarded clinically significant.

The 95% confidence interval of the fixed effect size will be used to assess whether the treatment difference reaches the minimally clinically important difference.

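### The cost endpoint subtracts DRG revenue and has no programme-cost term, so it tests a hospital net result and not the reduction in hospital cost named as the endpoint

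*Protocol article*

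**What the plan says.** The Abstract sets the aim: "we aim to ascertain whether a digital prehabilitation program can reduce perioperative morbidity and costs in patients undergoing major surgery". Secondary endpoints (Objectives {7}) lists cost reduction among the hospital cost effects of the app, and Outcomes {12} lists hospital costs as a secondary outcome.

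The cost paragraph of Outcomes {12} gives the daily rates: "Costs for a day on ICU are 1500€/day, for a day on the IMC 1000€, and on general ward 500" (euro). It then gives the rule: "The DRG generated by each case will be subtracted from the sum on each treatment unit and the final sums compared between the arms". Its scope statement reads: "The cost analysis will be conducted from the hospital/provider perspective based on in-hospital resource utilization including ICU, IMC, and general ward stay".

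Statistical methods for primary and secondary outcomes {20a} repeats the rates and the rule ("The DRG generated by each case will be subtracted from the sum on each treatment unit") and adds a two-sided t-test at p < 0.05. Neither section has a term for delivering the programme, which Trial design {8} describes as "The Prehab App and medical guidance".

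**The concern.** A cost endpoint should move when resource use moves, and only then. The planned quantity departs from this in two ways.

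1. It subtracts a revenue. Patients are randomised around the baseline visit (Sequence generation {16a}), while the DRG is generated by the later surgical case. The subtracted term is thus a post-randomisation quantity that may differ between arms. If it does, the test mixes a change in cost with a change in income.
2. It leaves out what the hospital spends on the programme in the intervention arm only. Whatever that amount is, the endpoint does not respond to it.

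At stake is how the cost result is read. A significant t-test could reflect revenue and not savings, a true bed-day saving could go unseen, or a saving could be reported before the cost of achieving it is deducted.

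**Working it through.** **The plan's own figure.** There is none to reproduce: the article gives no expected saving, standard deviation, power, DRG value, bed-day count or programme cost for this endpoint.

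**Inputs from the document.** ICU 1500, IMC 1000 and ward 500 euro per day; DRG subtracted per case; arms compared on the resulting sums (Outcomes {12} and Statistical methods {20a}).

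**Step 1: the rule as algebra.** Per case:

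endpoint = 1500 × ICU days + 1000 × IMC days + 500 × ward days − DRG

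Let D_bed and D_DRG be the differences in means (intervention minus control) of bed-day cost and DRG revenue, and K the hospital-borne programme cost per intervention patient beyond what controls receive.

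- Tested difference = D_bed − D_DRG
- Difference in hospital cost, programme included = D_bed + K
- Gap between the two = −(D_DRG + K)

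The tested difference equals D_bed only if D_DRG = 0, and it does not contain K.

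**Step 2: what a revenue difference does.** The bed-days here are assumed:

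- Control, 2 ICU, 2 IMC, 10 ward: 3000 + 2000 + 5000 = 10000 euro
- Intervention, 1 ICU, 1 IMC, 9 ward: 1500 + 1000 + 4500 = 7000 euro
- D_bed = 7000 − 10000 = −3000 euro

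| Assumed D_DRG (euro) | Tested difference (euro) | Reading |
|---|---|---|
| +1500 | −3000 − 1500 = −4500 | saving inflated |
| 0 | −3000 | saving shown correctly |
| −1500 | −3000 + 1500 = −1500 | half masked |
| −3000 | −3000 + 3000 = 0 | fully masked |
| −4500 | −3000 + 4500 = +1500 | reversed |

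Bed-day cost fell by 3000 euro in every row.

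**Step 3: what the missing programme cost does.** With the same D_bed and assumed K of 0, 500, 1500, 3000 and 4500 euro, D_bed + K is −3000, −2500, −1500, 0 and +1500 euro. The tested difference is the same for every K. In ward days at the plan's rate, an assumed K of 200 euro is 200/500 = 0.4 days and 1000 euro is 1000/500 = 2.0 days per patient.

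**Step 4: what belongs in K.** Only costs that are hospital-borne and specific to the intervention arm.

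- Hotline: Strategies to improve adherence {11c} provides it for every patient, so it cancels.
- Weekly contact: Outcomes {12} refers to weekly safety calls in both groups, so it largely cancels.
- Risk assessment: Methods for additional analyses {20b} analyses risk grouping in both groups, so at least part is shared.
- Ready4Op: given to both arms (Trial design {8}), so it cancels.
- Physician set-up of the training plan and review of exercise data: described for the app only (Intervention description {11a}), so it counts.
- App and smartwatch: specific to the intervention arm, but they count only if the hospital pays, which is not stated.

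**The case against.** **A net result is a legitimate provider measure.** The article declares a hospital perspective and restricts it to in-hospital resource use, so the scope is chosen openly. Cost minus revenue is worth reporting from that perspective. This stands, provided it is labelled as a net result. It does not turn the result into a cost, and a provider's view would also include what the provider spends on the programme. Background and rationale {6a} itself notes that prehabilitation is not reimbursed.

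**Subtracting the DRG allows for case mix.** Randomisation is already stratified by centre and diagnostic/surgical category, and surgical category is a planned covariate. Neither requires subtracting a payment that arises after randomisation.

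**The detail may lie in the analysis plan.** That plan is not shown, but the article fixes the formula and the test, and states the formula twice.

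Three stronger readings are tempting and are not supported:

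- *Everything in the programme is an uncosted extra of the intervention arm.* The hotline and weekly calls reach both arms, and who pays for the app and smartwatch is not stated.
- *Subtracting the DRG biases the comparison against the app.* The document does not say how DRG revenue responds to complications or length of stay, so neither direction nor size is known. With equal mean revenue the mean difference is unchanged.
- *The trial cannot answer the cost question at all.* Length of stay and ICU/IMC days are separate secondary outcomes and the rates are fixed, so gross bed-day cost can be recovered from data already collected. The problem lies in the sums the plan chooses to test.

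**Conclusion.** The point holds in this form: the tested quantity is a hospital net result on bed-day costs, whereas the named endpoint is a reduction in hospital cost. That follows from the stated formula without any assumption. The two coincide for bed-day cost only when mean DRG revenue is equal between arms, and the formula never includes hospital-borne cost specific to the intervention arm. That omission can only favour the app.

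The size cannot be computed from the document. The illustrated range of −4500 to +1500 euro around a true −3000 euro rests on assumed bed-days and assumed revenue differences. The 0.4 to 2.0 ward days rest on an assumed programme cost of 200 to 1000 euro. Only the daily rates come from the plan. This concerns one secondary endpoint; the primary endpoint and the sample size are untouched. It should be corrected before the cost data are analysed.

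**What to change.** In the cost paragraphs of Outcomes {12} and Statistical methods {20a}:

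1. Define the cost endpoint as gross bed-day cost: ICU, IMC and ward days times the stated rates, without subtracting the DRG.
2. Add the incremental hospital-borne programme cost to the intervention arm. If no unit cost can be agreed, show the result over a stated range of that cost. State who pays for the app and smartwatch. Items that both arms receive need no costing.
3. Report the difference in mean cost with a 95% CI.
4. Report cost minus DRG separately, labelled as the hospital net result.

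Bed-days and DRG are already inputs to the planned analysis, so the change needs revised wording and one new input, a unit cost for the programme. The drawback for the sponsor is that the reported saving may shrink.

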#### Translational substudies

In the setting of the LUMOS trial, translational substudies are included addressing the value of DNA, RNA, inflammatory markers, and possible other determinants for treatment outcomes. A fresh specimen of (tumor and) fatty (intraabdominal and subcutaneous) tissue should be preserved from every patient for secondary analysis in translational side projects to clarify the mechanisms and effects of exercising before surgery. Therefore, patient blood samples are drawn and analyzed pretherapeutically and during treatment. Formalin-fixed paraffin-embedded (FFPE) tumor specimens are centrally biobanked and analyzed. The biological substudies of the trial are designed for the validation of existing hypotheses and the discovery and generation of new hypotheses addressing important questions in prehabilitation and exercise research.

### Participant timeline {13}

See Table 1 and information on the intervention description.

### Sample size {14}

#### Sample size and power calculation

Based on findings from the literature and our pilot trial “Protego Maxima,” we observed an approximate complication rate or morbidity, as per the Dindo–Clavien classification, of 60% up to 90 days post-surgery [18]. Evidence from randomized-controlled trials suggests a relative reduction in morbidity due to prehabilitation ranging from 30 to 50% [19–21]. Hence, we estimated a clinically meaningful and feasible reduction to a complication rate (Clavien–Dindo I–V) of 45% at day 90 post-surgery in the intervention arm compared to the control arm. Potential center-related heterogeneity may influence the observed effect size. This will be addressed analytically by adjusting for center effects in the statistical models.

Given a study power of 80%, significance set at *p* < 0.05, and an anticipated dropout rate of 10%, we calculated a required sample size of 173 patients per treatment arm. We accounted for a dropout rate of 10% in our calculations. Utilizing the chi-square test and probability calculations in two groups led to a sample size of 191 patients per treatment arm (382 patients in total, including dropouts), in accordance with methods described by Rosner [22].

### Recruitment {15}

Patients will be recruited at all outpatient clinics of the enrolled centers. They are all university hospitals or maximum care centers, all undertaking several hundred major surgeries each year.

## Assignment of interventions: allocation

### Sequence generation {16a}

The patients will be randomized after eligibility confirmation, which will in most cases also be the baseline assessment day. The randomization sequence is computer-generated by an independent statistician using randomly varying block sizes and stratified by study center and diagnostic/surgical category. The allocation list is generated before study initiation and securely stored. For equal distribution of indications, sex, age, and center effects, we will create specific randomization blocks for the trial. The centers will receive envelopes with randomization information. The patients will be randomized during baseline assessment using block randomization stratified by study center and diagnostic/surgical category. This approach ensures balanced allocation of patients between treatment arms within each participating center and accounts for potential center-specific differences in surgical practice and perioperative care.

### Concealment mechanism {16b}

Allocation concealment is ensured using sequentially numbered, sealed envelopes prepared according to the computer-generated randomization list. Envelopes are opened only after written informed consent and completion of eligibility criteria and baseline assessments. Due to the nature of the intervention, participants and investigators are not blinded after allocation.

### Implementation {16c}

After signing the informed consent form, the randomization of the patient will be revealed by opening the randomization envelope and the group will be revealed to the patient and the researcher.

## Assignment of interventions: blinding

### Who will be blinded {17a}

Patients, researchers, and surgeons will not be blinded.

